# Development and Application of a Metaverse-Based Social Skills Training Program for Children With Autism Spectrum Disorder to Improve Social Interaction: Protocol for a Randomized Controlled Trial

**DOI:** 10.2196/35960

**Published:** 2022-06-08

**Keywords:** metaverse, social skills, Autism, ASD, digital therapy, Roblox, RCT, social skill, social interaction, human interaction, child, youth, development, wearable, biometric, communication, digital technology, eHealth, mhealth, stress, emotional change, online platform

## Abstract

**Background:**

Autism spectrum disorder (ASD) is characterized by abnormalities in social communication and limited and repetitive behavioral patterns. Children with ASD who lack social communication skills will eventually not interact with others and will lack peer relationships when compared to ordinary people. Thus, it is necessary to develop a program to improve social communication abilities using digital technology in people with ASD.

**Objective:**

We intend to develop and apply a metaverse-based child social skills training program aimed at improving the social interaction abilities of children with ASD aged 7-12 years. We plan to compare and analyze the biometric information collected through wearable devices when applying the metaverse-based social skills training program to evaluate emotional changes in children with ASD in stressful situations.

**Methods:**

This parallel randomized controlled study will be conducted on children aged 7-12 years diagnosed with ASD. A metaverse-based social skills training program using digital technology will be administered to children who voluntarily wish to participate in the research with consent from their legal guardians. The treatment group will participate in the metaverse-based social skills training program developed by this research team once a week for 60 minutes per session for 4 weeks. The control group will not intervene during the experiment. The treatment group will use wearable devices during the experiment to collect real-time biometric information.

**Results:**

The study is expected to recruit and enroll participants in March 2022. After registering the participants, the study will be conducted from March 2022 to May 2022. This research will be jointly conducted by Yonsei University and Dobrain Co Ltd. Children participating in the program will use the internet-based platform.

**Conclusions:**

The metaverse-based Program for the Education and Enrichment of Relational Skills (PEERS) will be effective in improving the social skills of children with ASD, similar to the offline PEERS program. The metaverse-based PEERS program offers excellent accessibility and is inexpensive because it can be administered at home; thus, it is expected to be effective in many children with ASD. If a method can be applied to detect children's emotional changes early using biometric information collected through wearable devices, then emotional changes such as anxiety and anger can be alleviated in advance, thus reducing issues in children with ASD.

**Trial Registration:**

Clinical Research Information Service KCT0006859; https://tinyurl.com/4r3k7cmj

**International Registered Report Identifier (IRRID):**

PRR1-10.2196/35960

## Introduction

Autism spectrum disorder (ASD) is a complex developmental condition that involves persistent challenges in social interaction, speech, and nonverbal communication, with restricted or repetitive behaviors [1]. In You’s study, deficits in social-emotional exchange, such as social communication disorder in interactions covering the present or past developmental period, are discussed along with deficits in nonverbal communication in social interaction and relationship formation appropriate to the developmental level. Impaired social functioning, which often requires lifetime treatment, is a characteristic of ASD [2]. Typically, school-aged children and adolescents acquire and develop the basic rules of social etiquette through observation of peer behavior or specific parental instruction [3]; however, some school-aged children with developmental disabilities, or some children and adolescents with ASD, have difficulties in acquiring the social etiquette necessary for peer relationships and they require additional intervention. As they lack social interaction skills, they are more likely to be isolated from their peers, making it evident that the etiquette necessary for relationships is lacking [4]. Furthermore, without treatment, many adults with ASD will have fewer interactions and friendships than an average person [5]. Imparting people with ASD the skills to make and retain friends to people with ASD is expected to have a lasting and significant impact on their lives. The prevalence of ASD has increased worldwide. Hong and Lee investigated the economic burden of ASD in South Korea using a nationally representative data source. The direct medical, nonmedical, and indirect costs resulting from ASD were estimated. The total prevalence was 5.04 (per 100,000 people) in 2008 and 10.97 in 2015. The economic cost of ASD was estimated at US $2,700,596 in 2008 and US $9,645,503 in 2015. The results of this study suggest that the increase in economic costs is greater than the increase in the prevalence [6]. Consultation with child psychiatrists for ASD diagnosis, psychological evaluation, and treatment, including ASD testing, are primarily available in cities, necessitating long waiting times and incurring high costs. Furthermore, even after diagnosis, treatments including speech therapy, psychotherapy, play therapy, and occupational therapy are centrally operated in cities, and treatment costs are high [7]. Therefore, appropriate treatment for many children with ASD is delayed. Furthermore, it is difficult for children from low-income families to receive timely diagnosis and treatment because of the high cost of treatment in facilities concentrated in cities.

Various treatment strategies for ASD include educational and behavioral interventions that target its core features. Well-designed interventions, such as risperidone and aripiprazole, have been reported to have strong and beneficial effects [8,9]. The Program for the Education and Enrichment of Relational Skills (PEERS) is a manualized evidence-based social skills program developed from ASD intervention programs [10]. The PEERS program used in this study has been designed to improve social and friendship skills in adolescents with high-function ASD. The results of a previous randomized controlled study examining the efficacy of PEERS in improving social abilities and friendship skills in high-functioning adolescents with ASD showed that the group involved in the program significantly improved its knowledge of social skills compared to the control group that was not part of the program. The frequency of meeting with friends increased and the overall social skills improved [11,12]. The Korean version of the PEERS social skills program appears to be effective for adolescents with ASD in Korea after modest adjustments for cultural differences. In a randomized controlled trial (RCT), participants who received the PEERS treatment showed significant improvement in social skill knowledge, interpersonal skills, state anxiety or depressive symptoms, as well as a decrease in ASD symptoms [2]. For adolescents with ASD who had previously received the PEERS program face to face, the program was suspended or postponed because of the COVID-19 outbreak, owing to the restrictions declared by many government statutes [13]. Children with ASD require continuous long-term training to improve their cognitive development and behavior. Due to the lack of social reciprocity and communication, special education teachers, regular training activities, and training locations are relatively fixed. However, the sudden COVID-19 outbreak disrupted the familiar and routine training activities of preschoolers with ASD, and limitations in the children’s physical environment may exacerbate behavioral problems [14]. Therefore, there is an increasing need to shift traditional therapeutic environments from face-to-face learning to internet-based play. According to the World Health Organization, telemedicine refers to the use of communication and virtual technologies to provide health care [15]. The advantages of telemedicine include the ability to receive treatment in a comfortable environment, ensuring continuity of care, low cost, high accessibility, and easy dissemination. Recent studies have shown that telemedicine interventions can improve the behavior of children with ASD [14,16-18]. Education was delivered using virtual reality (VR) technology to increase sociality for children and adults with ASD, and as a result, previous studies have reported improved sociality [19-21]. We designed the study to use a metaverse-based interactive game platform rather than VR equipment. Roblox, MineCraft, Whyville, and Zepeto are internet-based virtual world game platforms on which users can socialize, be creative, and play using their imagination [22,23]. Internet-based virtual world game platforms provide various types of cooperative activities in which children and adolescents can participate. Collaborative activities include solving problems and challenges, forming teams to execute missions through collaboration and organization, creating and decorating avatars, and practicing digital literacy skills, such as coding and writing. Internet-based multiplayer games can strengthen healthy communication and social connections as well as alleviate social isolation [24]. Playing games on internet-based gaming platforms can help foster a sense of belonging and develop friendships that are essential for the social and emotional development of children and adolescents. Developing a social skills training program using an internet-based virtual world game will be effective in improving social skills and will be an important treatment method during the COVID-19 pandemic situation, especially in the case of children and adolescents with ASD.

To improve the social skills of children with ASD, it is necessary to predict their anxiety early by collecting biometric information using wearable devices. Anxiety is a common problem in children, adolescents, and adults with ASD. Anxiety caused by emotion regulation impairments in children with ASD can lead to many behavioral problems, such as aggression and irritability [25]. Furthermore, problematic behavior, including self-harm in children with ASD, can be a significant barrier to accessing community services, including education, and can affect social improvement by limiting peer group formation or social participation in schools. Using wearable devices, early detection of abnormal signals in the biometric information of children with ASD, and conversion of problem behavior to prediction, mitigation, or alternative behaviors in advance will help improve children’s sociality.

The following are the objectives of this study: (1) developing a metaverse-based youth social skills training program using digital technology to improve the social interaction skills of children with ASD; (2) validating the effectiveness of the program developed as a metaverse for “Being a Good Sportsman,” which is part of the PEERS program, as well as validate the improvement of social interaction skills required by children with ASD; and (3) analyzing biometric information collected through wearable devices to confirm emotional changes in children with ASD during stressful situations.

## Methods

### Study Design

#### Summary

This study is a parallel randomized controlled study (trial registration: KCT0006859) involving children aged 7-12 years diagnosed with ASD who volunteered to participate in the study with the consent of a legal guardian. The study will include an intervention group and a control group at a 1:1 ratio. Participants will be publicly recruited through the internet to enroll in a clinical trial through the Korean-Wechsler Intelligence Scale for Children-IV (K-WISC-IV) test administered by a professional clinical psychologist. Following neuropsychological evaluation, the children eligible for this study will be assigned randomly to the intervention or the control group for 4 weeks. Randomization will be performed using the PROC PLAN method in the SAS software program (version 9.4, SAS Institute). In this study, we plan to develop and apply a social skills training program for children with high-function ASD that can be implemented within the metaverse platform based on the PEERS program using digital technology. The PEERS is a social skills training program developed for children with ASD who face difficulties in making or retaining friends. The PEERS program has 14 sessions. The 1st session gives the introduction and trading information; the 2nd session is about conversational skills; the 3rd session is on electronic communication; the 4th session is about choosing appropriate friends; the 5th session is regarding the appropriate use of humor; the 6th session is about peer entry strategies; the 7th session is regarding peer exit strategies; the 8th session is about get togethers, the 9th is on good sportsmanship; the 10th is about handling teasing; the 11th is on handling bullying and bad reputations; the 12th is regarding arguments and disagreements; the 13th is about handling rumors and gossip; and the 14th one includes a graduation party and ceremony [12]. Under the guidance of a clinical psychologist (with a PhD in education) and a clinical specialist in psychiatry, “Becoming a Good Sportsman,” which is part of the PEERS program, was selected and conducted as a proof-of-concept study. Socializing with peers is important for children and adolescents with ASD to build close friendships and engage in positive peer interactions. To reduce the burden of discussing a wide range of topics, it is better to proceed with activities that go well together. “Becoming a Good Sportsman” was selected because experts considered it suitable for a test study because it is composed of activity-based socializing to become a good sportsman, which corresponds to the ninth session selected in our study [26]. To maintain the consistency of the program, a professional clinical psychologist trained during the study period will conduct it. To verify the effectiveness of the program, the results of neuropsychological evaluation, including social development indicators and biometric information (heart rate, heart rate variability, saturation, respiratory rate, and stress index), will be collected through wearable devices. Children enrolled in the study will be randomized into 2 groups with the same baseline characteristics. To verify the effectiveness of the program, for each group, first the differences between the neuropsychological evaluation results, including the social development index determined before the experiment and the test results after the experiment, will be compared and analyzed using a statistical method. Second, the differences in the neurophysiological scores between the groups will be compared and analyzed. Based on the results of these 2 processes, the effectiveness of the metaverse-based social skills training program using digital technology will be verified.

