### Control Group

The control group will not intervene. Only neuropsychological tests will be conducted between the first and last week.

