### Statistical Analysis

All baseline variables will be summarized in a randomized group. Continuous data will be reported as means (SD) unless skewed and will be reported as medians (IQR). Before testing the effectiveness of the program, an independent sample *t* test and a Mann-Whitney U test will be performed to determine whether there are differences in demographic variables between the groups. To compare the effects of all outcomes, the analysis will be conducted using the paired *t* test and Wilcoxon signed rank test. To evaluate treatment effects in each group, ANOVA will be repeatedly performed for determining differences in variables between the baseline and posttest for the treatment and control groups, with a condition analysis using (treatment vs control) × time (baseline vs posttest). ANOVA will be performed to compare the effects of the program between the groups and to determine whether there is a significant difference between each group by judging the rejection range based on a significance level of 0.05. We plan to perform statistical analysis using Python (version 3.8.5) and R (version 4.0.4).

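### The Summary's effectiveness rule misnames the data for its only between-group step and lets within-group before-after change count towards the verdict

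*Protocol article*

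**What the plan says.** The rule stands in the protocol article under Methods, Study Design, Summary. Step 1 is a before-after comparison within each arm: "for each group, first the differences between the neuropsychological evaluation results, including the social development index determined before the experiment" are set against the results after the experiment. Step 2 is the only between-group step: "Second, the differences in the neurophysiological scores between the groups will be compared and analyzed". The conclusion is then drawn from both: "Based on the results of these 2 processes, the effectiveness of the metaverse-based social skills training program using digital technology will be verified".

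The Statistical Analysis section names the tests. Paired t and Wilcoxon signed rank tests are introduced with "To compare the effects of all outcomes". A repeated-measures ANOVA follows, "with a condition analysis using (treatment vs control) × time (baseline vs posttest"), and then "ANOVA will be performed to compare the effects of the program between the groups", judged at a "significance level of 0.05". Neither ANOVA is restricted to one kind of data.

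On what is measured in controls, the Control Group section says "Only neuropsychological tests will be conducted between the first and last week". The Methods paragraph of the Abstract assigns wearable devices to the treatment group. The Biometric Information section has every participating child wear one.

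**The concern.** The Summary is the only place that says how effectiveness will be established, so its wording matters more than that of a background sentence. It raises two problems.

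First, the data named for the randomized step do not match anything defined in the article. The questionnaire battery is called neuropsychological throughout, and the wearable signals are called biometric information. A reader applying the rule cannot tell from that sentence which data are to be compared between the arms.

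Second, step 1 gives uncontrolled before-after change a part in the verdict. The second study objective is to validate improvement in social interaction skills. Children this age mature, parents and children answer the same instruments again within weeks, and children enrolled with marked difficulties may regress towards the mean. Change inside one arm mixes all of this with any program effect. Only the contrast between randomized arms separates them.

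**Working it through.** **Reading the passages side by side**

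| Place in the article | Data | Comparison |
|---|---|---|
| Summary, step 1 | neuropsychological results | before-after, within each group |
| Summary, step 2 | *neurophysiological* scores (undefined) | between groups |
| Statistical Analysis, paired tests | all outcomes | before-after |
| Statistical Analysis, ANOVAs | not restricted | treatment × time, and between groups |
| Control Group | neuropsychological tests only | – |
| Abstract, Methods | wearable data, treatment group | – |
| Biometric Information | wearable data, all children | – |

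1. The Measures section describes the K-WISC-IV, K-SCQ, SRS-2, K-CBCL, K-VABS-2, SCL-R, CDI and RCMAS. None yields a neurophysiological score. The seven posttest instruments in Table 1 are this list without the K-WISC-IV.
2. The term in step 2 occurs once. Step 2 follows directly from a step on neuropsychological results, and the word *scores* suits questionnaires better than heart rate or oxygen saturation. This points to a slip.
3. If the Abstract and the Control Group section are right, controls have no wearable data, and a physiological comparison between arms cannot be made. Only the Biometric Information section makes it possible. The literal reading thus depends on a point on which the article disagrees with itself.
4. The Statistical Analysis section supplies the between-group comparison of the scores, but does not say which of its tests decides effectiveness. The Summary does say, and it counts both steps.

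**Why within-group tests should not decide: an illustration**

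The plan's own size reproduces: 2 groups × 12 (Sample Size section) = 24 (Screening and Inclusion Criteria). It states no effect size, SD or power. What follows rests on assumptions: two-sided 0.05, normal change scores, independent arms, and the same true change δ in both arms, so no program effect.

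For a paired t test with n = 12, df = 11 and critical value 2.201, the noncentrality is δ√12. With T a noncentral t variable:

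- P(significant) = P(T > 2.201) + P(T < −2.201)
- P(program arm significantly improved, control arm not significant) = P(T > 2.201) × [1 − P(significant)]

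| Shared δ (SD of change) | δ√12 | P(T > 2.201) | P(significant) | Program arm only |
|---|---|---|---|---|
| 0 | 0 | 0.025 | 0.05 | 0.025 × 0.95 = 0.02 |
| 0.3 | 1.039 | 0.156 | 0.16 | 0.156 × 0.842 = 0.13 |
| 0.5 | 1.732 | 0.353 | 0.35 | 0.353 × 0.647 = 0.23 |
| 0.8 | 2.771 | 0.714 | 0.71 | 0.714 × 0.286 = 0.20 |

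Under the same assumptions, a two-sample t test of the change scores rejects 5% of the time whatever δ is, because the shared shift cancels.

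**The case against.** The strongest reply is that this is a one-word slip in a summary paragraph, in an article with other language slips (the statement that the control group will not intervene is one). The Neuropsychological Test section says the battery is there to compare and evaluate effectiveness. The ANOVAs are planned, and the Summary sets no success threshold and no rule for combining its steps.

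Most of that stands. A reader might infer that no randomized comparison of the social and behavioral scores enters the verdict, or that a null between-group result on them could not count against the program. The documents do not support this. It requires taking literally a word that is probably wrong, and it passes over the treatment × time and between-group ANOVAs in the Statistical Analysis section. For the same reason the 16%, 35% and 71% figures do not measure this defect. They show how paired tests behave without a control.

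Two things remain. The physiological reading cannot be dismissed on the text alone: the Summary lists heart rate and other wearable signals among the data for verifying effectiveness, and the Biometric Information section puts the device on all children. And correcting the word leaves step 1 in place, with before-after change inside each arm still counted as evidence of effectiveness.

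**Conclusion.** The point holds as a fault in how the verdict rule is worded and built. It does not show a missing analysis. The rule names an undefined data type for its randomized step, probably in place of *neuropsychological*, and it lets within-group change contribute to a claim that such change cannot support. No figure in the article changes.

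The size cannot be put as an error rate of the plan, because the article does not say how the two steps combine and a between-group test is planned. The illustration shows the direction: with 12 per arm and equal true change in both, significant improvement in the program arm alone occurs in 13%, 23% and 20% of trials for assumed shifts of 0.3, 0.5 and 0.8 SD. A reader who took that pattern as support for the program would be misled that often on a single scale.

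The reading of the term as a slip is an inference from the surrounding text, and the sponsor should confirm it.

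**What to change.** In the Study Design Summary:

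- Redefine step 2 as the between-group difference in change of the neuropsychological scores, and identify it as the treatment × time comparison of the Statistical Analysis section.
- State that effectiveness is judged on that comparison, with within-group changes reported descriptively.
- Report any between-group comparison of wearable signals separately, as supportive.

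Reconcile the Abstract and the Control Group section with the Biometric Information section on whether controls wear the device, since this decides whether a wearable comparison between arms is possible at all.

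The cost is a few sentences. The scores are collected in both arms and the ANOVA is already planned. The downside is that the effectiveness claim becomes harder to meet: with 12 per arm, a two-sided 0.05 two-sample t test (df = 22, noncentrality 1.2 × √6 = 2.94) reaches 80% power only at a difference of 1.2 SD. That fits the article's own description of the trial as a pilot.
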